**Fig. 1 Fig1:**
[figure not shown]
Timeline cluster tool of the intervention

We adhere to the Standard Protocol Items: Recommendations for Interventional Trials (SPIRIT) guidelines in reporting the trial in this protocol (see Supplementary material, Fig. 1 and Table 2). Items from the WHO Trial Registration Data Set (TRDS) [35, 36] are provided in Table 1.

**Table 1 Tab1:** Items from the World Health Organization (WHO) trial registration data set

Data category	Information
Primary registry and trial identifying number	ClinicalTrials.gov, ID: NCT03565562
Date of registration in primary registry	11 June 2018
Secondary identifying numbers	Grant from the French Research Institute in Public Health: agreement 026/14
Source of monetary or material support	French Public Health Agency (*Santé Publique France*) in the frame of the primary prevention call for proposal of the French Research Institute in Public Health
Primary sponsor	Clinical Research Department, French National Institute of Health and Medical Research (INSERM), contact: [contact]
Secondary sponsor	None
Contact for public queries	Pr [name] ([contact])
Contact for scientific queries	Pr [name] ([contact]) and the PRINTEMPS team ([contact])
Public title	*Programme de Recherche INTerventionnelle et Evaluative Mené pour la Prévention du Suicide* (PRINTEMPS)
Scientific title	A cluster-randomized controlled trial of the local promotion of a smartphone application and associated website for the prevention of suicidal behaviors in the adult general population in France
Country of recruitment	France
Health conditions or problem(s) studied	Suicide, depression, psychological distress
Intervention	Intervention 1: tailored promotion of the e-health StopBlues program at the cluster level without involving general practitioners. Intervention 2: tailored promotion of the e-health StopBlues program at the cluster level with passive involvement of general practitioners through their waiting room. Control intervention: no promotion of the StopBlues program.
Key inclusion and exclusion criteria	Clusters: geographical areas with volunteer local authorities located in France (mainland and overseas territories) which provided a signed agreement to participate Participants: all adults living in participating clusters
Study type	Interventional study with randomized allocation, parallel assignment and no masking for prevention purpose
Date of first enrollment	22 August 2018
Target sample size	34 clusters for a total of more than 4 million adult inhabitants
Recruitment status	On-going
Primary outcome	Number of suicidal acts at the cluster level during a 12-month period, including deaths by suicide and suicide attempts. Data will be extracted from administrative databases.
Key secondary outcomes	Number of deaths by suicide and suicide attempts during a 24-month period Cost-effectiveness and budgetary impact analysis: fixed costs for the development of the promotion tools, semi-fixed costs for the implementation of the intervention, costs of suicidal acts, level of health-related quality of life and associated utility (validated questionnaire). For participants who used the StopBlues program: Effect on the intensity of the utilization of the StopBlues program by its users: number of downloads and connections for each zip code corresponding to local authorities included in the trial, time-lapse between the registration and the last connection to the StopBlues program for each user, proportion of users who came to know the program through the different communication channels, proportion of users who registered for a relative and not for themselves, proportion of users who completed a safety plan. Effect on the help-seeking behaviors of users of the StopBlues program and their participation in supportive activities: help-seeking and participation in supportive activities collected with an ad hoc questionnaire adapted from a validated one. Effect on the level of psychological impairment of the users of the StopBlues program: level of psychological distress, depression, anxiety, suicidal risk (validated questionnaires) (see Table 2 for more details)
Ethics review	Approved by the Ethics Committee of the French National Institute for Health and Medical Research (Approval n° 15–240 of 7 of July 2015). Approved by the French Advisory Committee for Data Processing in Health Research (Approval n° 15–793 of 30 September 2015). Approved by the French Data Protection Authority (Decision DR-2016-421 of 3 November 2016)

### Recruitment and eligibility

Thirty-four clusters will be recruited in France, through presentations of the research project in local authorities’ annual gatherings and through direct contact from the research team. Included local authorities, located in France (either mainland France or overseas territories), will be all those that volunteer to participate in the intervention, and which provide a signed agreement for participation in the research. Their list will be available upon request to the research team.

The StopBlues program will be freely available in the general population and, therefore, accessible by the populations of all local authorities involved in the trial.

### Sample size and power

The number of clusters was fixed by the identification of 34 clusters that agreed to be involved in the trial. The proportion of inhabitants who died from suicide or who made suicide attempts over a 12-month period was estimated to be 0.215% (personal data). We used an expected rate of 0.190% in the experimental group, which represents a reduction of 11.6%, slightly higher than the 10% global target supported by WHO for interventions on suicide [10]. In a two-arm, individually randomized trial, this would lead to a required number of participants of 1,229,350 to achieve a power of 80% with a Type I error rate of 2.5%. Type I error is set at 2.5% because two experimental groups are compared to the control group. Clustering also has to be taken into account. As the number of voluntary clusters was fixed, we calculated what the intraclass correlation coefficient (ICC) would be in order to achieve a power of 80% with our pre-specified number of clusters. Although we acknowledge that such an approach is not classical, it enables us to take into account feasibility reasons. Our mean cluster size equals 138,172 inhabitants and, therefore, randomizing 11 clusters in each arm allows for achieving 80% power if the ICC is around 10^−5^. Although this is a very low ICC, one has to keep in mind that clusters are geographical areas and ICCs are known to be lower in large clusters as compared to small ones. Moreover, ICC is known to depend on prevalence [37], with small ICC values for prevalence close to 0 or 1, and we expect very low rates (about 0.2%). As a consequence, we considered that a 10^−5^ ICC value would be appropriate in our trial.

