### Objectives of the trial

#### Primary objective

In this context, the primary objective of our trial (“*Programme de Recherche INTerventionnelle et Evaluative Mené pour la Prévention du Suicide*”, PRINTEMPS) is to assess the effectiveness of an intervention which includes a tailored, local-level promotion of the StopBlues program, and to compare the effectiveness of two types of local promotion (with or without a passive involvement of GPs through their waiting rooms) on deaths by suicide and suicide attempts over a 12-month period.

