## Methods/design

### Study design

This study will be implemented as a three-arm, parallel-group, cluster-randomized controlled superiority trial, with before-and-after observation. Cluster-randomization was deemed mandatory because of potential contamination issues. Indeed, the very nature of the intervention assessed (i.e., a promotion program) cannot be applied at the individual level. This is typically a cluster-cluster intervention, as defined by Eldridge et al. [32]. Clusters were defined as geographical areas sharing a common local authority. These local authorities can either be cities or a grouping of cities (“*communautés de communes*” or “*communautés d’agglomérations*”) based on the local health governance of each area. If several adjacent local authorities volunteer individually to participate in the trial, they will be considered as a unique local authority.

Clusters will be randomly assigned to one of the following three arms with a ratio of 1:1:1:
Arm 1: no promotion of the StopBlues program (*control group*)Arm 2: promotion of the StopBlues program by local authorities only (*basic promotion group*)Arm 3: promotion of the StopBlues program by local authorities with an additional passive involvement of GPs through their waiting rooms (*intensified promotion group*)

The initial trial duration will be of 12 months. Baseline data on the number of suicidal acts, collected 12 months prior to the intervention, will also be considered in each cluster. After a 12-month post-randomization period, clusters from the control group will be allowed for a further 12-month period to launch their promotional campaign supported by the research team through regular contacts and additional technical and financial resources in comparison to arms 2 and 3 (*more sustained promotion by local authorities*). This will facilitate the recruitment of clusters as well as their adherence to the intervention during the first 12-month period [33]. It will also enable us to determine whether promotion led by local authorities could be improved by supporting them in the provision of additional promotional resources.

A complete description of the different steps of the trial is presented in Fig. 1 using the Timeline cluster tool of Caille et al. [34].

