#### Statistical considerations

Characteristics of local authorities and of users of the StopBlues program will be described by the mean and standard deviation (SD) for continuous variables or by number (%) for categorical variables.

To assess the effectiveness of the intervention on the primary outcome (number of suicidal acts at the local authority level), we will compare the number of overall suicidal acts at 12 months and of suicides and suicide attempts separately between the trial arms adjusted on the number observed during the 12 months before the intervention.

We will use a Poisson regression analysis with clusters as analysis units and cluster size as offsets and adjust for baseline data and local authorities’ characteristics (population size, ecological index of deprivation, type of local authorities forming the cluster, etc.). A similar method will be used for all secondary outcomes measured at the level of local authorities.

For secondary outcomes measured on the users of the StopBlues program, mixed-model repeated-measures analyses will be used. This method will enable the inclusion of all users regardless of their level of adherence to the program, which will allow us to carry out the analysis despite some missing values. Adjustments will be made on the initial level of psychological distress of each user and on demographics. By using mixed-model repeated-measures analyses [61], we will also be able to account for potential clustering effects through the incorporation of adequate random effects for local authorities. Transformation of outcome variables will be done as necessary to meet distributional assumptions and to accommodate potential outlying observations. Additional subgroup analyses will be carried out to assess separately the effect of the intervention on users with a history of suicide attempts and those without.

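### The primary objective includes intensified versus basic promotion, but the 2.5% level and the sample size cover only the two comparisons with control

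*Protocol article*

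**What the plan says.** The primary objective, in the section of that name and again in the abstract, has two parts. One is the effectiveness of local promotion of the program. The other is "to compare the effectiveness of two types of local promotion (with or without a passive involvement of GPs through their waiting rooms"), judged on deaths by suicide and suicide attempts over 12 months. With a control arm and two promotion arms allocated 1:1:1, that makes three pairwise contrasts.

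The section on sample size and power counts two: "Type I error is set at 2.5% because two experimental groups are compared to the control group". It compares 0.215% under control with 0.190% in a single experimental group, a relative reduction of 11.6%. It obtains 1,229,350 participants for two individually randomized arms at 80% power, and concludes that "randomizing 11 clusters in each arm allows for achieving 80% power if the ICC is around 10^−5". It gives no difference, level or power for intensified against basic promotion.

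The outcome section and the registration table name one primary outcome, the count of suicidal acts. Under statistical considerations the primary analysis is described thus: "we will compare the number of overall suicidal acts at 12 months and of suicides and suicide attempts separately between the trial arms". No order or other multiplicity rule is given.

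**The concern.** The protocol controls multiplicity and says why it chose 2.5%, and that reason leaves out one of the contrasts in its own primary objective. This is not a detail left for an analysis plan: the stated rationale and the stated objective do not match.

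Two things follow. First, if the head-to-head is tested at the same 2.5%, the set of primary claims is no longer held at 5%. Second, using one rate for both promotion arms implies a head-to-head difference of zero, so its power is undefined at the planning values. If the true added effect of the waiting-room component is modest, a non-significant result is the likely outcome, and it would say little about whether that component helps.

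**Working it through.** **Inputs.** All are from the section on sample size and power: control rate p1 = 0.215%, promotion rate p2 = 0.190%, level 2.5%, power 80%, mean cluster size m = 138,172, 11 clusters per arm, ICC about 10^-5. The head-to-head rates in step 4 and the effect patterns in step 5 are assumptions.

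**1. The plan's sample size.** With p̄ = 0.2025%, z(0.9875) = 2.2414 and z(0.80) = 0.8416:

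n = [2.2414·√(2p̄(1−p̄)) + 0.8416·√(p1(1−p1) + p2(1−p2))]² / (p1−p2)² = 614,678 per arm, or 1,229,356 in total.

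The protocol gives 1,229,350, so the figure reproduces with a two-sided 2.5% level. A one-sided 2.5% level would give 1,015,154.

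**2. The plan's ICC.** Inhabitants per arm: 11 × 138,172 = 1,519,892. Design effect: 1,519,892 / 614,675 = 2.473. ICC: (2.473 − 1) / 138,171 = 1.07 × 10^-5, which matches the stated order of magnitude.

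**3. Family-wise error on the composite, each contrast at 2.5%.**

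- Two contrasts with control: bound 2 × 2.5% = 5%.
- Three pairwise contrasts: bound 3 × 2.5% = 7.5%; if they were independent, 1 − 0.975³ = 7.3%.
- The contrasts share arms and so are correlated. Simulating three arm means with equal variance under the global null (4 million draws) gives 4.6% for two contrasts and 6.4% for three.

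**4. Head-to-head power.** At ICC 10^-5 the design effect is 1 + 138,171 × 10^-5 = 2.382, so the effective size per arm is 1,519,892 / 2.382 ≈ 638,150. With SE = √[(pa(1−pa) + pb(1−pb)) / 638,150], power at a two-sided 2.5% level is Φ(Δ/SE − 2.2414).

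| Contrast | Δ | SE | Δ/SE | Power |
|---|---|---|---|---|
| 0.215% vs 0.190% (planned, against control) | 0.0250% | 0.00796% | 3.14 | 82% |
| 0.2025% vs 0.190% (basic has half the planned effect) | 0.0125% | 0.00783% | 1.60 | 26% |
| 0.190% vs 0.1805% (a further 5% reduction) | 0.0095% | 0.00761% | 1.25 | 16% |
| 0.190% vs 0.168% (a further 11.6%) | 0.0220% | 0.00748% | 2.94 | 76% |

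Power of 80% is reached at about 0.167%, a further 12.1% reduction beyond basic promotion. At ICC 1.07 × 10^-5 the figure is 12.3%. Either is slightly larger than the 11.6% planned for promotion against none.

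**5. A closed test.** With three arms, any two of the pairwise null hypotheses together imply the global null. A global test at 5% followed by each pair at 5% therefore controls the family-wise error over all three contrasts. Simulation with each arm's own variance p(1−p)/638,150 gives 5.0% under the global null, and these powers:

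| Pattern of effects | Contrast | 2.5% each | Closed test |
|---|---|---|---|
| Both promotions at 0.190% | either vs control | 82% | 85% |
| Only one promotion works | that one vs control | 82% | 86% |
| Basic 0.2025%, intensified 0.190% | intensified vs control | 82% | 80% |
| Same | basic vs control | 24% | 33% |
| Same | intensified vs basic | 26% | 35% |

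These are large-sample normal results with the variance taken as known. With about 11 clusters per arm the real levels will differ somewhat, but the comparison between procedures is like for like.

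**The case against.** The strongest reply is that the damage is limited. Each comparison with control keeps its 2.5%, its sample size reproduces, and adding the head-to-head moves the family-wise error only from 4.6% to 6.4%. That is fair, and it is why the point is not graded higher. It does not remove the mismatch between the objective and the reason given for the level.

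A second reply is that the number of clusters was fixed by the 34 volunteers, which the protocol discloses, so no head-to-head target could have changed the size. That also stands. What can be asked for is a statement of the detectable difference. The low powers rest on assumed differences; a larger added effect would fare better (76% for a further 11.6%).

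A reader might go further and infer three primary outcomes, hence nine primary tests, because suicides and attempts are also compared separately. The documents do not support that. The abstract, the registration table, the outcome section and the statistical section all name the combined count as the primary outcome, and nothing says that a component alone could carry a claim. The separate comparisons read as ordinary reporting of a composite's parts.

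Nor does the protocol plan to treat a null head-to-head as proof of no added benefit. It declares a superiority trial, so that misreading is a risk to guard against and not a stated intention.

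**Conclusion.** The point holds for the head-to-head on the composite. It belongs to the primary objective, yet the 2.5% rationale and the sample size leave it out. Tested at 2.5% alongside the two control contrasts, it takes the family-wise error to about 6.4% (bound 7.5%). Its power is unstated and, under the modest added effects assumed here, is about 16% to 26%. The power figures rest on the plan's own cluster size, 11 clusters per arm and ICC of 10^-5, and on head-to-head rates that the protocol does not supply.

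It would be wrong to conclude that the sample size calculation is in error: 1,229,350 is right for the single contrast it addresses. The planned tests against control are not undermined either. This is a should-fix matter.

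**What to change.** Choose one of two routes and write it down before outcome data are analysed.

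- **Keep the head-to-head primary.** Use a closed procedure on the 12-month composite: a global three-arm test at 5%, then each of the three pairwise contrasts at 5%. Replace the sentence that ties 2.5% to two comparisons. The cost is that no pairwise claim is possible if the global test fails, and that intensified versus control loses 1 to 2 points of power when basic promotion has half the effect. In the other patterns examined, power against control rises. A plain 1.67% per contrast would also control the error, but lowers the planned power against control from 80.0% to 75.5% at ICC 1.07 × 10^-5.
- **Make the head-to-head a secondary objective.** The 2.5% rationale and the sample size then stand as written.

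On either route, state the head-to-head power or detectable difference, report that contrast with its confidence interval, and say that a non-significant result will not be read as no added benefit. Add a line labelling the separate analyses of suicides and of attempts as supportive; that is a clarification of wording and not the correction of a further error. None of this needs more clusters or data.

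### Testing both contrasts with control at a flat 2.5% is valid, but a Holm step-down gives more power at the same implied 5% family-wise error

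*Protocol article*

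**What the plan says.** The protocol article's *Sample size and power* section sizes a single two-arm contrast "to achieve a power of 80% with a Type I error rate of 2.5"%, and gives the reason for that level: "Type I error is set at 2.5% because two experimental groups are compared to the control group". No other significance level appears in the article. The 5% being divided, and whether the tests are two-sided, are not stated.

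The same section supplies the remaining inputs: a control rate of 0.215%, one experimental rate ("We used an expected rate of 0.190% in the experimental group"), a "required number of participants of 1,229,350" under individual randomization, and the statement that "randomizing 11 clusters in each arm allows for achieving 80% power" if the intraclass correlation is around 10^-5. The number of clusters was fixed by those that volunteered.

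Under *Statistical considerations* the primary analysis is a cluster-level Poisson regression, in which "we will compare the number of overall suicidal acts at 12 months and of suicides and suicide attempts separately between the trial arms". That section gives no test level and no step-down or hierarchical rule. The *Primary objective* also asks how the two types of promotion compare with each other.

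**The concern.** Read plainly, each promotion-versus-control contrast is tested at 2.5% whatever the other shows. Once one contrast is significant at 2.5%, a 5% family-wise error allows the other to be tested at 5%, and the flat rule leaves that unused. It also takes no account of the correlation of about 0.5 that a shared control arm induces under 1:1:1 allocation, which step-down Dunnett does use.

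This matters more here than in most trials because power cannot be bought with more clusters. The intraclass correlation was also solved backwards from the clusters available, so the 80% has little slack. What is at stake is efficiency, chiefly the chance of showing that each type of promotion beats control. The validity of the test is not in question.

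**Working it through.** **1. Reproduce the plan's figure.** Inputs from *Sample size and power*: p1 = 0.00215, p2 = 0.00190, power 80%, level 2.5%.

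- n per arm = (z_alpha + z_beta)^2 × [p1(1 − p1) + p2(1 − p2)] / (p1 − p2)^2
- Variance term: 0.0040417675. Difference: 0.00025.
- Two-sided 2.5%: z = 2.2414 + 0.8416 = 3.0830, so n = 614,674 per arm and 1,229,349 in total, against 1,229,350 stated.
- Two-sided 5%: z = 1.9600 + 0.8416 = 2.8016, total 1,015,147. This does not reproduce.

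The stated size therefore rests on two-sided 2.5% per contrast.

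**2. Clustering.** "Our mean cluster size equals 138,172 inhabitants", so 11 clusters give 11 × 138,172 = 1,519,892 per arm. Design effect available: 1,519,892 / 614,675 = 2.473. Implied intraclass correlation: 1.473 / 138,171 = 1.07 × 10^-5, in line with the stated order of magnitude. At that value each contrast has 80% power at 2.5%.

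**3. Joint power.** Assumptions: both promotion arms reach 0.190% (the article gives one experimental rate), the two test statistics are bivariate normal with mean 3.083 each, and their correlation is 0.5. Let c1 = 2.2414 (two-sided 2.5%) and c2 = 1.9600 (two-sided 5%).

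- P(Z1 > c1, Z2 > c1) = 0.6872
- P(Z1 > c1, Z2 > c2) = 0.7328
- Flat 2.5%, both shown: 68.7%
- Holm, both shown: 2 × 0.7328 − 0.6872 = 77.8%
- Holm, a given contrast: 0.8000 + (0.7328 − 0.6872) = 84.6%
- At least one, either rule: 0.8000 + 0.8000 − 0.6872 = 91.3%

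| | Flat 2.5% | Holm |
|---|---|---|
| A given contrast | 80.0% | 84.6% |
| Both contrasts | 68.7% | 77.8% |
| At least one | 91.3% | 91.3% |
| Family-wise error, no effect in either arm | 4.6% | 4.6% |
| False rejection of an ineffective arm when the other works | 2.5% | 4.2–4.3% |

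Simulations of 2 million draws agree. Step-down Dunnett (first critical value 2.212) gives 78.0% for both.

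**4. Sensitivity.**

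- *Correlation 0 to 0.7:* power for both goes from 64.0–71.3% (flat) to 75.1–79.4% (Holm), a gain of about 8 to 11 points.
- *Unequal effects:* if one arm has the planned effect and the other half of it (means 3.083 and 1.542), the stronger contrast moves from 80.0% to 80.6%. The weaker moves from 24.2% to 32.8%.
- *Larger intraclass correlation:* at 10^-4 the design effect is 1 + 138,171 × 10^-4 = 14.82 and the mean falls to 1.259. Power for both goes from 6.5% to 10.6%, a gain of about 4 points from a very low base.

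**The case against.** The strongest reply is that the 2.5% stands only in the sample-size section. A sponsor who meant to use Holm would plan at 2.5% too, because that is Holm's first step, and a statistical analysis plan that is not shown could name a step-down rule. This stands in part. A reader might infer that the article forbids testing the second contrast at 5%; it does not say so. A flat 2.5% is the plain reading of the only level given, and the analysis section offers nothing that changes it.

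Second, Bonferroni is valid. This stands in full. A reader might infer that the sample size or the error control is wrong. Neither is: the required number reproduces, and Holm needs no change to it.

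Third, the largest gain concerns showing both promotions effective, which the plan does not set as a power target. This also stands. It would be wrong to say that the trial loses nine points of power for its planned criterion. The planned criterion is 80% per contrast; there the gain is 4.6 points under equal effects and under 1 point for the stronger arm when effects differ markedly.

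Fourth, Holm is not free. The false rejection rate for an ineffective arm rises when the other arm works, though it stays within 5% family-wise.

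Fifth, the 2.5% and 5% steps hold only for a family of two. The *Primary objective* includes the comparison between promotions. If that is confirmatory, Holm over three contrasts would start at 5%/3 = 1.67%.

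**Conclusion.** The point holds as one of efficiency. A flat 2.5% per contrast controls the implied 5% family-wise error but is dominated by Holm, which rejects everything Bonferroni rejects whatever the effects, the correlation between contrasts or the intraclass correlation.

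The size of the gain does depend on assumptions: both arms at 0.190%, an intraclass correlation near 10^-5, contrasts correlated at 0.5, and a normal approximation with 11 clusters per arm. Under these, power per contrast rises by 4.6 points and power for both by about 9 points, with no change in power for at least one. The figures cover only the two contrasts with control and take the unstated family-wise level to be 5%.

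**What to change.** Keep 2.5% as the planning level; the sample-size paragraph needs no recalculation. In *Statistical considerations*:

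- State that the confirmatory family is the two promotion-versus-control contrasts on total suicidal acts, at a two-sided family-wise level of 5%.
- State that they are tested by Holm: the smaller p-value at 2.5% and, if significant, the other at 5%. Step-down Dunnett with small-sample critical values is an equivalent or slightly better alternative.
- Say whether the comparison between the two promotions is confirmatory. If it is, replace the rule above with a closed or step-down procedure over all three contrasts.
- Say which confidence intervals will be reported, since intervals that match a step-down test are less simple than Bonferroni intervals.

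The cost is a few sentences, to be settled before outcomes are compared by arm. No data or clusters are added. The price is a higher false rejection rate for an ineffective arm when the other works (2.5% to about 4.3%), still within the 5% family-wise limit.
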